While interventions should be developed for patients with all severities of COPD, it is logical to target immediate efforts towards patients with ‘high-risk’ COPD, that is, those who are at most risk of exacerbation and hospital admissions. Established data indicate that patients with COPD who have had severe exacerbation (one requiring ED attendance or hospital admission) in the previous 12 months and/or have persisting hypercapnic respiratory failure requiring home NIV fall into this high-risk group.^6 13^ Interventions proven in this group can then be rolled out (if cost-effective) to the lower risk groups of patients with COPD.

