## Study methods and analysis

### Study design

This study is a prospective observational cohort hybrid implementation and effectiveness study.^26^ It will be performed according to the UK Policy Framework for Health and Social Care Research (2020).^27^ The clinical intervention component is regarded as a phase IV adoption study. Data visualisation to facilitate guideline-based care, supported self-management and home NIV are evidence-based COPD interventions.

In this study, we will evaluate the adoption of digitally integrated remote management service innovations to support routine clinical care. Implementation of these will be evaluated and the digital innovations will be iterated to optimise them, based on user experience accrued during the study. We will acquire a consented dataset for trial endpoint analysis including exploratory machine learning-based predictive modelling. The machine learning analysis will also allow us to prioritise data inputs for follow-up study.

Secondary outcomes for the RECEIVER cohort will be compared with those from matched cohorts of patients acquired from the NHS GG&C SafeHaven dataset. Ethics approval is in place to access this large database of de-identified data, to establish a control cohort from a historical time series and a RECEIVER trial concurrent time series. These cohorts will be matched for demographics, COPD severity and hospital admission frequency with the RECEIVER cohort.

We will conduct a substudy of additional baseline and follow-up physiological measurements (oscillometry, parasternal electromyography (EMG), home pollution monitoring) in patients in whom it is feasible to obtain these during their hospital admission and/or hospital attendance alongside their routine clinical care.

Additionally, we will conduct a substudy of clinical users, with platform tracking analytics to measure clinician time spent on the platform, and user experience data. Clinical team members involved in the delivery of patient support using the digital service will be eligible for inclusion and appropriate consent will be sought. The qualitative components will be acquired through semistructured group or 1:1 interviews conducted by trained members of the research team. Thematic analysis will be performed. Anonymised transcripts will be coded, and themes generated from the codes. Themes will be discussed within the research team to reach agreement and add rigour.

An overview of the study design is provided in figure 2.

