### Study population

People with high-risk COPD attending secondary care in the North and South Sectors of NHS GG&C will be screened for inclusion in this study.

Inclusion criteria:

Confirmed diagnosis of COPD, established prescreening or at screening, defined as per Global Initiative for Chronic Obstructive Lung Disease (GOLD) 2020 guidelines.^6^Home NIV cohort: hypercapnic respiratory failure and/or sleep disordered breathing, meeting established criteria for provision of home NIV.Exacerbation cohort: presentation within last 12 months with severe or life-threatening exacerbation of COPD, defined as per GOLD 2020 guidelines.^6^Participant or close contact who has daily access to smartphone, tablet or home computer with internet access.Informed consent.>18 years of age.

Exclusion criteria:

Inability to comprehend informed consent.Communication barrier precluding use of COPD digital service.

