### Screening and eligibility assessment

Participants will be identified from ED attendance, hospital admission or COPD multidisciplinary team referral. It is anticipated that the majority of participants will be identified and recruited during their index acute admission.

Review of focused medical history and lung function test results will be undertaken as part of screening evaluation to ensure all inclusion and no exclusion criteria are met.

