## Data collection

### Data collection by research team

#### EHR data

The following data will be obtained from EHRs held within NHS GG&C SafeHaven: demographic, coded diagnosis list, Charlson Comorbidity Index, Scottish Index of Multiple Deprivation quintile, medication history, laboratory results, lung function results, ED attendance, hospital admission, pulmonary rehabilitation attendance data from 1 January 2010 onwards. These data will be presented for evaluation in a study machine learning analysis platform.

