## Statistics and data analysis

Secondary outcomes in the RECEIVER observational cohort will be compared with matched retrospective data from de-identified linked datasets of historical control and contemporary control high-risk patients with COPD. These will comprise of patients identified from coding and admission data as having had severe exacerbation of COPD between 1 January 2010 and 30 April 2019 (historical cohort) and between 1 July 2019 and 30 June 2020, excluding participants enrolled in the RECEIVER Study (contemporary control). The historical control dataset will contribute to machine learning models development. Secondary outcome analysis will be separately compared between the RECEIVER cohort, historical cohort and contemporary control cohort. This component of the study is also separately registered with dataset access approval from NHS GG&C SafeHaven LPAC.

The clinical endpoint data will be reported as a proportion and 95% CI for that outcome, calculated by Kaplan-Meier method. Demographic data will be presented as mean and SDs, or medians and IQRs as appropriate. Correlation, t-test, analysis of variance and effect size analyses will be used as appropriate for secondary endpoint analysis, comparing results of clinical endpoint and patient-centred outcomes with NIV therapy and supported self-management parameters.

Machine learning ensemble methods will be used to develop binary classification problems for patient risk. Precision, recall, accuracy and C-statistics of the receiver operating characteristic curve will be used to evaluate model performance.

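### Participants can enter on an ED attendance without admission, but the control source and matching variables do not secure the same index event in the controls

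*Protocol article*

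**What the plan says.** **Participants.** The Introduction describes high-risk patients as those with a "severe exacerbation (one requiring ED attendance or hospital admission) in the previous 12 months", or with hypercapnic failure needing home NIV. The exacerbation-cohort criterion under Study population is "presentation within last 12 months with severe or life-threatening exacerbation of COPD, defined as per GOLD 2020 guidelines"; the text shown does not require admission. Under Screening and eligibility assessment, "Participants will be identified from ED attendance, hospital admission or COPD multidisciplinary team referral". The next sentence adds: "It is anticipated that the majority of participants will be identified and recruited during their index acute admission".

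**Controls.** Under Statistics and data analysis, the historical controls are patients "identified from coding and admission data as having had severe exacerbation of COPD between 1 January 2010 and 30 April 2019". The same wording covers the contemporary controls, with a window of 1 July 2019 to 30 June 2020 and RECEIVER participants excluded.

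**Matching.** Under Study design: "These cohorts will be matched for demographics, COPD severity and hospital admission frequency with the RECEIVER cohort".

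**Data available.** The SafeHaven extract listed under EHR data includes "lung function results, ED attendance, hospital admission, pulmonary rehabilitation attendance data from 1 January 2010 onwards".

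**The concern.** The same term, severe exacerbation, defines entry on both sides of the comparison, but the stated route to it differs. For participants it includes an ED visit that ended in discharge. For controls the named source is diagnostic coding and admission records. The article elsewhere lists ED attendance and admission as separate items: in the Introduction, in the screening sources, in the SafeHaven extract and in Table 1 under unscheduled care. Read against that usage, admission records would not naturally pick up patients who were never admitted.

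At stake are the secondary comparisons with the two SafeHaven cohorts: clinical events (including admission and mortality) and occupied bed days. The projected cost savings in Table 1, which rest on reduced admissions, could be affected too. If the RECEIVER cohort contains a type of index event that the controls lack, part of any difference reflects how patients were selected and not what the service did.

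**Working it through.** There is no planned figure to reproduce: under Sample size the article declines a power calculation, and it gives no ED-only share. The check is therefore a comparison of definitions, followed by an illustration of scale.

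**1. Does matching repair the gap?** Take a participant whose qualifying event was ED-only and who had no admission in the matching period, and suppose controls are found through admissions.

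- If the matched admission frequency counts the index event, every such control has at least one admission and the participant has none. There is no match.
- If it excludes the index event, the participant can be paired with a control whose only admission was the index one. The pair then has unlike index events.

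The article does not say which applies.

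**2. Mismatched branch, no true service effect.** Let f be the ED-only share of the RECEIVER participants compared. Let r be the later admission rate of ED-only participants relative to admitted patients. Both are assumptions. Then

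apparent rate ratio = (1 − f) × 1 + f × r = 1 − f(1 − r).

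For f = 0.20 and r = 0.5: 1 − 0.20 × 0.5 = 0.90.

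| f | r = 0.5 | r = 0.7 | r = 0.85 | r = 1.0 | r = 1.2 |
|---|---|---|---|---|---|
| 0.05 | 0.975 | 0.985 | 0.993 | 1.00 | 1.01 |
| 0.10 | 0.95 | 0.97 | 0.985 | 1.00 | 1.02 |
| 0.20 | 0.90 | 0.94 | 0.97 | 1.00 | 1.04 |
| 0.30 | 0.85 | 0.91 | 0.955 | 1.00 | 1.06 |
| 0.40 | 0.80 | 0.88 | 0.94 | 1.00 | 1.08 |

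Matching on severity and admission frequency may bring r closer to 1. The home NIV cohort can enter without an exacerbation, so f over all participants is smaller than the ED-only share within the exacerbation cohort.

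**3. Scale against sampling error.** Assume a 12-month admission risk of 60% after an admitted event and 35% to 45% after an ED-only event. The spurious gap is f × (0.60 − ED-only risk):

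- f = 0.1, risk 0.45: 0.1 × 0.15 = 1.5 points
- f = 0.2, risk 0.35: 0.2 × 0.25 = 5.0 points
- f = 0.3, risk 0.35: 0.3 × 0.25 = 7.5 points

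With 400 per side and 1:1 matching (no ratio is stated), the standard error of the difference is about √[(0.60 × 0.40 + 0.525 × 0.475)/400] = 0.035, or 3.5 points. The gaps are then roughly 0.4 to 2.1 standard errors. Since 400 is the whole planned cohort, it is an upper limit for the number compared; with fewer, the same gap is fewer standard errors. These inputs all assume a lower ED-only risk, so they exclude zero bias by construction.

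**4. Unmatched branch.** If ED-only participants drop out, this mechanism gives a ratio of 1.00. The cost is sample: with all 400 in the comparison, 380 remain at f = 0.05, 320 at f = 0.20 and 240 at f = 0.40. The result then describes only admitted patients.

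**5. Direction by endpoint.** Table 1 sets bed days in the preceding 12 months against the following 12. If the index stay falls in the preceding period, admitted controls carry bed days there that ED-only participants do not. The controls would then show the larger fall, which works against the service. The sign need not be the same across endpoints.

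**The case against.** A reader might infer that ED-only participants are bound to be set against admitted controls and that the comparison therefore favours the service. The documents do not support that, for four reasons.

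- The control definition uses the same term, severe exacerbation, and does not say that controls must have been admitted. Coding is undefined and could include ED diagnosis codes. The control component is separately registered under its own dataset approval, where the extraction rules may sit.
- Where ED-only participants go unmatched, the bias disappears. In the mismatched branch it favours the service on later admissions only if ED-only patients have lower later risk, and no figure in the article shows this.
- Most participants are expected to be recruited during an index admission, and some patients identified in the ED will then be admitted. The ED-only share may be small.
- The primary endpoint, utilisation, has no control comparison. The Study limitations section concedes a general risk of bias and disclaims definitive proof.

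All four points stand as limits on direction and size. They do not close the gap. The article itself fixes the control source, in words narrower than its participant definition, and fixes the matching variables without index-event type. The general acknowledgement of bias does not mention this mismatch, which can be avoided with data already requested.

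**Conclusion.** The concern holds in a limited form. Following the article as written does not ensure that participants and controls share the same kind of index event, and the named matching variables do not repair this. ED-only participants may be compared with admitted controls or may be lost from the matched analysis. A lower apparent rate of later admissions under the service is the more plausible direction in the first case, but it rests on the assumption r < 1. With r = 1 there is no bias, and with r > 1 it reverses.

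For ED-only shares of 5% to 40% and r of 0.5 to 0.85, the spurious rate ratio runs from 0.993 down to 0.80; none of these inputs comes from the documents. The effect is confined to the secondary controlled comparisons.

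**What to change.** Under Statistics and data analysis, select both control cohorts with the Introduction's definition of severe exacerbation, using the ED attendance records in the SafeHaven extract ("lung function results, ED attendance, hospital admission") as well as admissions. Add index-event type, ED-only versus admitted, as a matching or stratification variable. Like events are then compared with like, whether or not the matched admission count includes the index event.

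If ED diagnosis coding proves too incomplete to identify COPD exacerbations, restrict the RECEIVER side of the controlled comparison to participants whose qualifying event was an admission. State that restriction, and report how many participants it removes.

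The cost is one more selection query on data already requested and one more matching variable. The fallback also means a smaller comparison set and a conclusion limited to admitted patients.

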## Study outcome measures

Primary and secondary endpoints for the RECEIVER Study are shown in table 1.

**Table 1 T1:** RECEIVER primary and secondary endpoints

Primary endpoint	Proportion of enrolled high-risk participants with COPD who use remote management in a digital service model
Secondary endpoints	Clinical outcomes, comparing impact of digitally enabled remote management versus historical and contemporary SafeHaven cohorts: Clinical events: COPD exacerbation; unscheduled care contact (digital platform, COPD team visit, primary care, emergency department, hospital admission); mortality—COPD and non-COPD related. Hospital occupied bed days preceding and subsequent 12 months (adjusted time interval if survival <12 months). Treatment uptake (where indicated): smoking cessation; pulmonary rehabilitation; vaccination; supported self-management; home oxygen; home NIV. NIV group: NIV usage, symptom change, NIV therapy parameters, blood gases during routine clinical care. Supported self-management: utilisation of self-management information (page views), number of exacerbation managed at home versus in hospital, number of rescue packs used in 12 months (captured through weekly PROs), utilisation of messaging (number of message threads), sputum microbiology (where available during routine clinical care), impact of patient activation measures (where measured during routine care). Impact of demographics, physiology and patient activation measures (where measured during routine care)—deprivation category of area of residence, age and sex, number of previous admissions, smoking status, participation in pulmonary rehabilitation in previous 2 years; lung function measurements, modelled home air pollution exposure; EMG, oscillometry and home air pollution monitoring in subset of participants where this is carried out—on outcomes, clinical events and treatment uptake. Clinical service outcomes for digital service model, remote-managed home NIV and supported self-management: Remote-managed home NIV: number, nature and complexity of NIV therapy reviews and interventions to provide. Supported self-management: number, nature and complexity of reviews and interventions to provide. Digitalised service model: user and developer time/cost required for development and modification of clinical dashboard; qualitative analysis (clinical user satisfaction and reflection on efficiency or additional workload); quantitative analysis (clinical dashboard utilisation tracking). Patient portal: user and developer time/cost required for development and modification of clinical dashboard; qualitative analysis (user satisfaction) and quantitative analysis (uptake, engagement with app and wearable, successful use of digital service vs bypass to conventional healthcare contacts). Machine learning-supported exploratory analyses of associations and relative predictive importance of electronic health record, PROs, wearable physiology and NIV parameters: Associations between changes in PROs (MRC, CAT, symptom diary, and EQ-5D-5L questionnaires) with routine clinical care interventions, COPD exacerbation and other clinical events. Associations between changes in wearable monitoring parameters (activity, sleep, heart rate variability, energy expenditure, respiratory rate) with routine clinical care interventions, COPD exacerbation and other clinical events. Associations between changes in NIV-monitored parameters (usage, leak, airway pressures, respiratory rate, tidal volume, minute ventilation, inspiratory/expiratory ratio and detected respiratory events) with routine clinical care treatment interventions, COPD exacerbation and other clinical events. Associations between changes in clinical endpoints and relative importance plots of all remote management-acquired data (including EMG, oscillometry and home pollution monitoring exploratory endpoints in subgroup these measured on) to determine contribution of these to outcome prediction, and therefore value of these for future prospective study. Patient-centred outcomes: Health-related quality of life (EQ-5D-5L) at baseline and monthly during study. Qualitative user research (planned subset of participants, convenience sample) with semistructured user experience interviews. Impact of patient activation (where this is measured at baseline and/or follow-up during routine clinical care) on enrolment and use of digital service model. Healthcare cost analyses: Development and installation costs for digitalised service model for remote management of COPD. Recurring costs (clinical staffing, digital platform hosting, digital platform scheduled update and maintenance) for digital service model for remote management of COPD. Projected direct and indirect cost-savings (admission and unscheduled care reduction, travel, carer burden impact, clinical efficiency) of high-risk COPD with digitally enabled remote management, compared with previous service model.

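### Historical controls can be indexed from the first day of the data extract, so those indexed in 2010 cannot have the full preceding 12 months that the bed-day endpoint needs

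*Protocol article*

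**What the plan says.** Four statements in the Protocol article bear on this.

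- **Statistics and data analysis:** historical controls are patients with "severe exacerbation of COPD between 1 January 2010 and 30 April 2019 (historical cohort". Contemporary controls come from 1 July 2019 to 30 June 2020. Each cohort is compared with RECEIVER separately.
- **EHR data:** a list of SafeHaven items, including ED attendance, ends with "hospital admission, pulmonary rehabilitation attendance data from 1 January 2010 onwards".
- **Table 1 (Study outcome measures):** among the clinical outcomes compared with the SafeHaven cohorts is "Hospital occupied bed days preceding and subsequent 12 months (adjusted time interval if survival <12 months". A separate item, on factors that may influence outcomes, includes "participation in pulmonary rehabilitation in previous 2 years".
- **Study design:** the control cohorts are "matched for demographics, COPD severity and hospital admission frequency with the RECEIVER cohort".

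The only interval adjustment given is the one for short survival in the bed-day endpoint. The article states no run-in, no exclusion of early index dates and no period over which admission frequency is counted.

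**The concern.** The extract and the historical control window open on the same day. Followed as written, a control whose index exacerbation falls in 2010 has between 0 and 364 days of recorded history, yet the bed-day endpoint asks for 12 months. The survival adjustment does not help, because it shortens follow-up after the index and not the history before it. If admission frequency is also counted over 12 months, the matching variable is truncated in the same way.

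The gap falls on one side only. The trial starts in September 2019 (Abstract), so participants have more than nine years of data behind them. At stake is the historical comparison of bed days and admissions. This matters because the Sample size section projects a reduction of one admission per patient per year.

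**Working it through.** The plan gives no figure of its own to reproduce. The check is date arithmetic, followed by a simulation for the direction of bias.

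**Inputs from the article:** control window 1 January 2010 to 30 April 2019; data from 1 January 2010; bed-day look-back 12 months; contemporary window from 1 July 2019.

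**Step 1, window length.** 2010 to 2018 is 9 × 365 + 2 leap days = 3287 days. January to April 2019 adds 120, giving 3407 days.

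**Step 2, share with a short look-back.** Index days with fewer than 365 days of prior data: 365. Share = 365 / 3407 = 10.7%.

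**Step 3, size of the shortfall, with index dates spread evenly (assumption).**
- 2010 controls: mean prior data = (0 + 364) / 2 = 182 days; 182 / 365 = 49.9%. At a steady rate of bed days, about 50% of the preceding total is not seen.
- Whole cohort: (365 × 182 + 3042 × 365) / 3407 = 345.4 days; 345.4 / 365 = 94.6%. The under-count is about 5%.

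**Step 4, the other groups.** From 1 January 2010 to 1 July 2019 is 3287 + 181 = 3468 days, so every contemporary control has a full look-back. So does every participant.

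**Step 5, direction of the matching bias.** Severe exacerbations were simulated from a gamma-Poisson model. The assumptions, which are not in the article, are: 60,000 patients per setting, constant rates with mean 1 or 2 per year and gamma shape 1 or 2, and no deaths or new diagnoses. The index is a random exacerbation in the window. The table gives later 12-month events in controls matched on recorded history, relative to controls matched on true history.

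| Handling of unobserved history | Matched at | 2010 controls | All historical controls |
|---|---|---|---|
| Counted as no events | 1 or 2 prior events | 19% to 54% more | 2% to 5% more |
| Counted as no events | 0 prior events | 41% to 74% more | 6% to 12% more |
| Annualised over observed time, index event included | 2 or 3 per year | 12% to 38% fewer | 1% to 4% fewer |

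For example, with mean 1, shape 1 and one prior event, zero-filling gives 1.344 / 1.008 = 1.33 in 2010 controls. Annualising at 2 per year gives 0.773 / 1.008 = 0.77.

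**Step 6, sensitivity to the index definition.** If the index were each patient's first exacerbation in the window, 56% to 76% of controls would be indexed in 2010 under the same assumptions. Patients who enter the population later would lower that share.

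**The case against.** **The direction of bias.** A reader might infer that the gap biases the comparison towards RECEIVER. The article does not support that as a general statement. It is true if missing history is read as no admissions: 2010 controls then carry a higher underlying rate than their recorded count suggests, and their before-after change in bed days looks worse. But admission frequency may equally mean a rate over observed time, and Step 5 shows that the matching bias can then reverse. It disappears if short-history patients are dropped. Nor should the two mechanisms be added together: controls matched on recorded prior admissions will tend to show recorded prior use like the participants', so they overlap.

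**The data start.** A reader might also infer that SafeHaven holds nothing before 2010. The article says only what will be obtained. The date could even be attached to the rehabilitation item alone, though it more naturally covers the whole list. That section also describes the data as feeding a machine learning platform.

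**The index date.** The control dates define who belongs to the cohort; no index event is defined. A patient with exacerbations in 2010 and 2016 could be matched at the later one. This limits how many controls are affected, but nothing excludes the 2010 event.

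**Rehabilitation history.** The two-year item is not a stated matching variable and may describe participants only. A two-year look-back would be short on 730 / 3407 = 21.4% of index days, but that figure matters only if a control analysis uses the item.

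**Detail left elsewhere.** The control component is separately registered with its own data access approval, and that specification may contain a look-back rule. A missing rule alone would not be a finding. What stands is that the dates the article does fix do not fit the endpoint it states. The feasibility aim in Study limitations lowers the stakes but does not resolve that.

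**Conclusion.** The point holds as an unhandled look-back gap in the historical comparison. Any control indexed in 2010 lacks the full preceding 12 months required for bed days, and lacks a full matching history if matching uses 12 months.

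With evenly spread index dates and a steady rate, the gap touches 10.7% of the window. It under-counts preceding bed days by about half in 2010 controls and by about 5% overall, so the pooled effect is small. It could be much larger if the first exacerbation in the window is the index. The direction is conditional on how unobserved time is treated. The contemporary comparison is untouched because the cohorts are compared separately, and the primary endpoint, which measures use of the service, does not involve controls.

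**What to change.** Either start historical index dates on 1 January 2011, or keep the present window and obtain SafeHaven data from 1 January 2009 if they exist. In both cases, require at least 12 months of observable data before every control index date. The same text should name the index event and the period over which admission frequency is counted. Require 24 months only for a control analysis that uses the two-year rehabilitation history.

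The cost is one date in the extract or cohort specification. If earlier data cannot be obtained, the window falls from 3407 to 3042 days, a loss of 10.7%. Patients whose only qualifying exacerbation was in 2010 drop out; those with a later one can be indexed there. With earlier data, nothing is lost.
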